## Secondary endpoints:

1. Safety profile

1. CMV disease

2. Opportunistic infections,

3. PTLD

4. Hyperlipidemia

5. Wound healing problems

6. Lymphoceles

1. Requirement for additional immunosuppression (such as corticosteroids, antimetabolites or other immunosuppressive agents)
2. Acute rejection per kidney biopsy (Banff grading criteria)
3. ATN (acute tubular necrosis) rate (requirement for dialysis within 7 days post-transplant)
4. Graft survival
5. Patient survival
6. Immunological parameters
7. New onset BK virus per kidney biopsy
8. **Describe the follow-up of subjects and identify any procedures that are performed exclusively for research purposes, or performed more frequently than would normally be clinically indicated (e.g. additional or more frequent radiologic evaluations).**

All participants will follow the standard post-transplant schedule for routine laboratory testing.

For safety purposes, subjects will have surveillance biopsies at 6, 12, and 24 months. The renal biopsy at 24 months following transplant is performed exclusively for research purposes. Subjects who present with a condition, either medically or anatomically, that would present a greater risk to the subject, may at the discretion of the Principal Investigator forego a kidney biopsy. It is standard practice at this center to request surveillance biopsies for renal transplant recipients who are not receiving steroids as part of their maintenance immunosuppression.

Participants will return for study visits at 1, 3, 6, 12, and 24 months and as needed in accordance with standard schedule for all transplant patients. Long-term data regarding graft and patient survival, incidence of allograft rejection, serious adverse events, CMV disease, opportunistic infections, PTLD, hyperlipidemia, wound healing problems, lymphoceles and immunosuppression regimen will be collected at years 3, 4, and 5 from a review of the subject’s medical record.

To measure the long-term effect of rATG, CD3 and CD4/CD8 counts with ratio will be done at baseline, two weeks post transplant, 1, 3, 6, 12, and 18 months, and annually to year 5. These tests are performed for research purposes.

Participants may be asked to have this additional blood drawn in order to test for certain immunological parameters. This will depend on whether or not the patient is able to return to the transplant center at the required intervals. The investigator, in consultation with the patient and the study coordinator, will determine if this is possible.

The following blood tests will be performed to determine if T-cells are being re-educated in the thymus following rATG administration:

- Transglutaminase expression will be measured 1 hr post-initiation of first dose of rATG.

● Serum levels of ε (γ-glutamyl)-lysine diisopeptide will be measured every other day for 7 days post-transplantation then weekly until pre-transplant levels are reached.

● TREC output will be measured weekly, until levels return to baseline, beginning 2 days post-completion of rATG therapy.

● CD3 counts will be measured daily until total counts are > 100.

● Gene array analyses for assessment of functional signal transduction pathways and analysis of cell surface phenotypes of peripheral blood leukocytes will be performed at 1, 3, 6, and 12 months post-transplantation.

**e. Describe briefly the statistical methods used to analyze the data.**

Binomial and numerical outcomes are described using proportions and means, respectively, and are compared using chi-square test or Fisher’s exact test when appropriate and t test, respectively. Graft survival and acute rejection rates are determined using Kaplan-Meier estimates and are compared using log-rank tests. The effects of covariates on the hazard risk of graft survival and acute rejection are evaluated using a Cox proportional hazard model.

A mixed-model for repeated measures is used to compare calculated GFR values to examine the effect of single versus divided-dose rATG on kidney function. A linear mixed-model of repeated measures is used to examine the relationship between the amount of rATG infused at the time of reperfusion and calculated GFR during the follow-up period.

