- Transglutaminase expression will be measured 1 hr post-initiation of first dose of rATG.

● Serum levels of ε (γ-glutamyl)-lysine diisopeptide will be measured every other day for 7 days post-transplantation then weekly until pre-transplant levels are reached.

● TREC output will be measured weekly, until levels return to baseline, beginning 2 days post-completion of rATG therapy.

● CD3 counts will be measured daily until total counts are > 100.

● Gene array analyses for assessment of functional signal transduction pathways and analysis of cell surface phenotypes of peripheral blood leukocytes will be performed at 1, 3, 6, and 12 months post-transplantation.

All participants will follow the standard post-transplant schedule for routine laboratory testing.

For safety purposes, subjects will have surveillance biopsies at 6, 12, and 24 months. If future funding becomes available, a renal biopsy at year 5 may be added. (If this becomes feasible, the protocol will be amended and an addendum consent form will be prepared for the subjects.) Subjects who present with a condition, either medically or anatomically, that would present a greater risk to the subject, may at the discretion of the Principal Investigator forego a kidney biopsy. Banff scoring will be utilized to categorize rejection and transplant nephropathy. It is standard practice at this center to request surveillance biopsies for renal transplant recipients who are not receiving steroids as part of their maintenance immunosuppression.

Participants will return for study visits at 1, 3, 6, 12, and 24 months and as needed in accordance with standard schedule for all transplant patients. Long-term data regarding graft and patient survival, incidence of allograft rejection, serious adverse events, CMV disease, opportunistic infections, PTLD, hyperlipidemia, wound healing problems, lymphoceles and immunosuppression regimen will be collected at years 3, 4, and 5 from a review of the subject’s medical record.

Adverse Events:

All adverse events will be monitored and recorded. These will include both events related to the safety profile of the study drugs (CMV disease, Post-Transplant Lymphoproliferative Disorder [PTLD], opportunistic infections, elevated lipids, etc.) and expected renal transplant complications (wounds, lymphoceles, diabetes, weight gain, etc.). All unexpected adverse events and any deaths will be reported to the IRB per UNMC policies.

Endpoints:

Primary endpoints:

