**c. What are the specific subject withdrawal criteria?**

Criteria for subject withdrawal from this study include:

- Withdrawal of consent by the subject at any time during the course of the study
- Second transplant after initial kidney transplant (i.e. pancreas and liver)
- Graft loss
- Subject is lost to follow-up
- Pregnancy
- Patient experiences an unmanageable adverse event
- Death of subject
- Study is terminated

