**1) What is the frequency of data analysis?**

A formal interim analysis of the accumulated study data was conducted after accrual of 60 subjects and again at 140 subjects. The findings of the second 140 subject interim analysis were peer-reviewed and published in the journal *Transplantation*. Outcome data are continually being collected and audited as subjects progress through the initial subsequent phases of the study. An additional formal analysis of the induction phase will be performed at the accrual of the final study subjects. The optimal timing of a formal analysis of the outcome of the calcineurin inhibitor withdrawal phase will be defined as further experience of calcineurin inhibitor withdrawal accumulates.

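### Item 10e names time-to-event methods only for graft survival and acute rejection, leaving patient survival, CMV disease, opportunistic infection and PTLD to raw proportions despite unequal follow-up

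*Protocol*

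**What the plan says.** Protocol item 10e gives one rule for yes/no outcomes: "Binomial and numerical outcomes are described using proportions and means, respectively, and are compared using chi-square test", with Fisher's exact test as the alternative. It then names two exceptions: "Graft survival and acute rejection rates are determined using Kaplan-Meier estimates and are compared using log-rank tests". The Cox sentence covers the same two: "The effects of covariates on the hazard risk of graft survival and acute rejection are evaluated using a Cox proportional hazard model".

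The secondary endpoints in item 10c list "Patient survival" separately from graft survival, and list CMV disease, opportunistic infections and PTLD under the safety profile. Item 10e names none of these four.

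On follow-up, the protocol says:
- Item 10c: long-term data on patient survival, CMV disease, opportunistic infections and PTLD, among others, "will be collected at years 3, 4, and 5 from a review of the" medical record.
- Item 15c: withdrawal criteria include withdrawn consent, graft loss, a second transplant and "Subject is lost to follow-up".
- Item 10g: information is gathered only while the graft functions or until death.
- Item 3b: a 10% drop-out is planned for.
- Item 15e(1): "An additional formal analysis of the induction phase will be performed at the accrual of the final study subjects".

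**The concern.** The plan uses methods that handle censoring for graft survival and acute rejection. In the same subjects, with the same censoring, the only method it states for death, CMV disease, opportunistic infection and PTLD is one that ignores time under observation. A subject seen event-free for one month then either counts the same as one seen event-free for five years or is dropped, depending on the denominator. Both choices bias the risk.

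The protocol draws safety conclusions from outcomes of this kind. Item 19b reports no detected difference in patient survival or in rATG-related adverse events. Items 11b(3) and 15d describe drug-related risks or adverse events as statistically the same between arms. Those two items do not name CMV disease or PTLD rates as their basis, so the direct link is with patient survival. For the infections and PTLD, what is at stake is whether the reported risks are right.

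**Working it through.** The protocol gives no event rate for these outcomes and no length of accrual, so it has no figure to reproduce. The only stated input is the 10% drop-out (item 3b). Event risks, accrual length and unequal loss are assumptions. Item 3b dates the power analysis to July 2005 and calls the document a five-year re-write, with accrual not yet complete, so an accrual of several years is plausible.

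**1. Drop-out alone, all subjects in the denominator.** Let F be the true risk over the period and d the proportion lost, with independent exponential times. Put a = −ln(1−F) and c = −ln(1−d). The crude proportion is

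crude = a/(a+c) × [1 − (1−F)(1−d)].

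- F = 10%, d = 10%: 0.5 × (1 − 0.81) = 9.5%, which is 5% too low in relative terms.
- F = 20%, d = 10%: 0.679 × (1 − 0.72) = 19.0%, again about 5% too low.
- For d = 5%, 20% and 30%, and F from 2% to 20%, the relative understatement is about 2.5%, 10% and 15–16%.

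**2. Same data, complete-case denominator** (events plus subjects followed to the end): crude / [crude + (1−F)(1−d)].

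- F = 10%, d = 10%: 0.095/(0.095 + 0.81) = 10.5%.
- F = 20%, d = 10%: 0.190/(0.190 + 0.72) = 20.9%.

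The direction reverses, so it depends on the denominator.

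**3. Staggered entry, all subjects in the denominator, no drop-out.** Assume uniform accrual over A months, analysis at last accrual, constant hazard, and a true 24-month risk of 15%. A share 24/A of subjects has follow-up spread evenly over 0 to 24 months; the rest have the full 24. The mean risk in the first share is 1 − 0.15/[−ln(0.85)] = 1 − 0.15/0.1625 = 7.7%.

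- A = 60: 0.4 × 7.7% + 0.6 × 15% = 12.1% (19% too low).
- A = 48: 0.5 × 7.7% + 0.5 × 15% = 11.4% (24% too low).
- A = 72: 0.333 × 7.7% + 0.667 × 15% = 12.6% (16% too low).

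**4. Comparison between arms.** With equal true risks and equal loss, the formula in step 1 gives the same value in both arms, a false difference of 0. With an assumed 5% loss in one arm and 20% in the other:

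- F = 10%: 9.75% versus 8.98%, a difference of 0.8 points.
- F = 20%: 19.5% versus 18.0%, a difference of 1.5 points.

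**The case against.** Item 10e answers a form question that asks for a brief description. It does not list which outcomes are binomial and gives no denominator or time point. A statistical analysis plan, not at hand, may supply these. Nothing in item 10e bars a proportion at a fixed time among subjects who reached it. This has force against any claim about what the analysts will do. It has less against the text: item 10e does allot time-to-event methods by outcome, and it leaves patient survival out while naming graft survival.

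A reader might infer more than the protocol supports:
- **That subjects not followed count as event-free, so risks are understated.** No sentence says so, and step 2 shows the opposite direction under another denominator.
- **That new-onset BK virus is equally affected.** It is defined on kidney biopsy, biopsies are scheduled at 6, 12 and 24 months, and BK is not in the year 3 to 5 list. A proportion among those biopsied at each time is defensible.
- **That long-term risks will be badly understated at final accrual.** That analysis is described as one of the induction phase, and no passage says that 24-month or five-year risks will be read from it as crude proportions. Step 3 therefore illustrates what could happen and does not forecast it.
- **That the comparison is biased.** Randomised arms share the accrual pattern, and step 4 shows no false difference without unequal loss.

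The objection is also right about competing events. In a cumulative incidence analysis, subjects who die or lose the graft first stay in the denominator, as they do in a raw proportion over all subjects. The gain comes from handling loss and unequal observation time. Plain Kaplan-Meier for infections and PTLD would tend to overstate risk.

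**Conclusion.** The point holds for patient survival, CMV disease, opportunistic infection and PTLD. The only method item 10e states that can apply to them is a raw proportion, while the protocol's own terms make follow-up unequal. Followed as written, this gives biased risks, in a direction that depends on an unstated denominator.

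The size is modest on the protocol's own figure: about 5% relative understatement at 10% drop-out with all subjects counted, or about 5% relative overstatement with complete cases. It grows to 16–24% for a 24-month risk of 15%, but only under assumed uniform accrual over 48 to 72 months, a constant hazard and analysis at last accrual. A false difference between arms of about 0.8 to 1.5 points needs an assumed 5% versus 20% loss. These are secondary endpoints, so the change is advisable but not critical to the primary comparison.

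**What to change.** Extend the time-to-event sentence in item 10e along these lines: patient survival is estimated by Kaplan-Meier and compared by log-rank test; time to first CMV disease, opportunistic infection and PTLD is estimated as cumulative incidence at fixed times, with death and graft loss as competing events, and compared by Gray's test.

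Keep chi-square or Fisher's exact test for outcomes fully observed at a fixed time, such as dialysis within 7 days, and for BK virus among subjects biopsied at each scheduled time (6, 12 and 24 months).

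Because item 15c withdraws subjects at graft loss, the sentence should also say how deaths after graft loss enter the patient survival analysis; Kaplan-Meier does not correct for censoring that is related to risk.

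The cost is some wording and a little more analysis work. It needs no more subjects or procedures, and event dates should be available from the medical records already being reviewed.

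### Daily CD3, weekly TREC and late diisopeptide sampling stop on the subject's own value, but item 10e offers only means and t tests for them

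*Protocol*

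**What the plan says.** Protocol Section II, item 10c, repeated in item 10d, lists blood tests meant to show whether T-cells are re-educated in the thymus after rATG. Three have a stopping rule that depends on the result:

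- CD3, daily series: "CD3 counts will be measured daily until total counts are > 100".
- TREC: "TREC output will be measured weekly, until levels return to baseline, beginning 2 days post-completion of rATG therapy".
- Diisopeptide: "will be measured every other day for 7 days post-transplantation then weekly until pre-transplant levels are reached". The first 7 days are fixed, and only the weekly part stops on the value.

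The same items also set a fixed CD3 schedule that does not depend on recovery: "CD3 and CD4/CD8 counts with ratio will be done at baseline, two weeks post transplant, 1, 3, 6, 12, and 18 months", then annually to year 5.

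Item 10e gives the analysis: "Binomial and numerical outcomes are described using proportions and means, respectively, and are compared using chi-square test", with Fisher's exact test as the alternative for proportions and the t test for means. It adds: "Graft survival and acute rejection rates are determined using Kaplan-Meier estimates and are compared using log-rank tests". Cox models are named for those same two outcomes, and mixed models for calculated GFR. No time-to-recovery analysis is named for any immunological marker. Immunological consequences of the two rATG regimens are secondary goal 1, and immunological parameters are a secondary endpoint.

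**The concern.** When the measured value ends a subject's series, the information lies mainly in when the series ends. Item 10e covers these markers only through its general rule for numerical outcomes, and each natural way of applying that rule has a weakness.

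- **Values compared by sampling day.** Once recovery begins, the subjects still sampled are those who have not recovered. For daily CD3, all their earlier values are at or below 100 by construction. The faster arm loses more subjects, so the two means are drawn into the same range.
- **Days to recovery compared by t test.** A subject who leaves unrecovered has no value. The plan makes this foreseeable: item 15c withdraws subjects for graft loss, death, loss to follow-up and withdrawn consent, and items 10c and 10d make the additional immunology draws depend on whether the patient can return.

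Duration of depletion is a quantity of interest here. The background (item 2) reports more prolonged lymphocyte depletion with a short course that has a higher initial dose. At stake is a real difference in reconstitution that the analysis shrinks or misses.

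**Working it through.** The protocol gives no effect size or power for these markers, so there is no figure to reproduce. The mechanism was checked by simulation.

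**Inputs from the protocol.** 180 subjects in a 2 x 2 factorial (item 10a), so 180 / 2 = 90 per rATG regimen; the CD3 stop at the first value above 100; means and t test (item 10e).

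**Inputs assumed.** Recovery day T is log-normal with log-SD 0.5. On day t, CD3 = 10 + 90 x t/T plus noise of SD 10. Two-sided alpha is 0.05, with 2000 runs and no drop-out.

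**Daily CD3, medians 7 versus 9 days, days before the two-week visit:**

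| Day | Still sampled | Difference, still sampled | Difference, all subjects | Ratio | t-test power, still sampled | t-test power, all |
|---|---|---|---|---|---|---|
| 3 | 89 / 90 | 9.1 | 9.7 | 0.94 | 0.79 | 0.80 |
| 5 | 77 / 85 | 9.4 | 16.1 | 0.58 | 0.67 | 0.84 |
| 7 | 54 / 70 | 7.4 | 22.5 | 0.33 | 0.41 | 0.87 |
| 10 | 26 / 43 | 5.2 | 32.2 | 0.16 | 0.17 | 0.87 |

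A rank test on the day of first CD3 above 100 has power 0.89. With equal medians, rejection rates are 0.05 to 0.06, so the effect is attenuation and lost power, not false positives.

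**Other assumed curves.**

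- Medians 7 versus 10 days, same curve: power among those still sampled is 0.98, 0.94, 0.72 and 0.31 at days 3, 5, 7 and 10. It is 0.98 to 0.99 with all subjects sampled, and above 0.99 for time to recovery.
- Medians 7 versus 10 days, step-shaped recovery with exponential times: 0.07 to 0.09 among those still sampled, 0.19 to 0.40 with all subjects, and 0.55 for time to recovery.
- Medians 9 versus 12 days: 0.88, 0.75 and 0.43 at days 5, 7 and 10, against 0.94 for a log-rank test of time to recovery. A t test on days to recovery has similar power when everyone recovers; its weakness is the subjects who do not.

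**Fixed CD3 visits.** At two weeks and later every subject is scheduled, so the stopping rule selects nobody at those visits.

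**TREC start by arm.** Sampling begins 2 days after rATG ends. A 24-hour infusion ends on day 1, so the first sample is at about 1 + 2 = day 3. Four alternate-day doses, taken here as days 0, 2, 4 and 6, give 6 + 2 = day 8. The weekly grids are then 3, 10, 17 and so on versus 8, 15, 22 and so on. A true recovery on day 9 is recorded on day 10 in one arm and day 15 in the other; a recovery on day 12 is recorded on day 17 versus day 15. A plain log-rank test from transplantation reads this offset as a treatment difference. With no true difference (90 per arm, log-SD 0.5), it rejected in about 51%, 24%, 14% and 9% of runs for assumed median recovery of 9, 14, 21 and 30 days. It came near 5% only when recovery took about two months or more.

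Diisopeptide is timed from transplantation in both arms, so its grids coincide and this problem does not arise.

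**The case against.** The strongest reply is that item 10e asks only for a brief description. It does not mention these markers, and it does not say that a t test is run on each sampling day. A reader might infer that the plan prescribes such day-by-day tests; the text does not support that. A t test on days to threshold, or a chi-square test on the proportion recovered by a given day, fits the same sentence without restricting the comparison to slow recoverers. A statistical analysis plan that is not shown may settle the summary measure.

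Much of this stands, and it makes the loss conditional. It does not remove the point: item 10e assigns numerical outcomes a method by class, and that method has no provision for a series that stops on its own value or for a subject who never reaches the threshold.

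A reader might also infer that CD3 sampling ends at recovery, so that all later CD3 comparisons are distorted. The fixed schedule to year 5 rules this out; only the extra daily draws stop. Nor do the documents plan any equivalence claim on these markers, so a formal finding of equal reconstitution cannot be attributed to them.

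Finally, it is fair to object that a log-rank test for all three series would create a new error for TREC. That objection holds and shapes the remedy.

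**Conclusion.** The point holds for three series only: daily CD3, weekly TREC, and diisopeptide after day 7. For these, the method class in item 10e can understate a regimen difference if values are compared by day, and cannot handle unrecovered subjects if days to recovery are compared. The direction follows from the protocol's own rules; the size does not. Under the assumed curve with medians 7 versus 9 days, the observed CD3 difference is 94% of the full one at day 3 and 16% at day 10, with power of 0.79 and 0.17. Only CD3 was simulated for this loss, so no size is claimed for TREC or diisopeptide. The simulations assume complete sampling of 90 per regimen, which the reliance on patients' ability to return makes optimistic. These are secondary, mechanistic endpoints, and no trial decision is tied to them, so this is a minor but worthwhile correction.

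**What to change.** In item 10e, state that for daily CD3, weekly TREC and diisopeptide the outcome is time to the recovery criterion.

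- **Daily CD3 and diisopeptide:** Kaplan-Meier and log-rank. Censor subjects who have not recovered at their last sample, and say how death, graft loss, withdrawal and missed draws are treated.
- **TREC:** an interval-censored time-to-recovery comparison that allows for the arm-specific start of weekly sampling, not a plain log-rank test from transplantation.
- **Markers measured at fixed times in all subjects,** including CD3 and CD4/CD8 on the fixed schedule: keep means and t tests.

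The cost is a few sentences and slightly more analysis work for TREC. No additional samples or data are needed, and Kaplan-Meier and log-rank are already in the plan; the interval-censored method would be new.
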